### 2.2. Study Design

The current study is designed as a longitudinal, participant-blinded, sham-controlled, cluster randomized controlled trial (RCT) with a nested qualitative evaluation. The RCT study includes three-assessment periods over the course of six months, while the nested qualitative study involves an additional semi-structured interview two weeks after completing the treatment or placebo sessions.

The protocol for this RCT is based on the Standard Protocol Items: Recommendations for Interventional Trials (SPIRIT) 2013 Checklist [31] (Table 1). The study design and flowchart of the protocol, following the CONSORT 2010 standards [32], are summarized in Figure 1. The study will be conducted in three major hospitals in the North of Portugal with multidisciplinary diabetic foot consultations, and was approved by the Ethics Committee of the three hospitals. The study is also registered on the ClinicalTrials.gov platform since the 7th of January 2021 (Registration number: NCT04698720).

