### 2.4. Randomization

All eligible patients will be randomly assigned to one of the four groups—TG1, TG2, ACG, or PCG—in varying size blocks so that, over time, all groups can have a similar number of participants [36,37]. An independent researcher (Researcher 4), unaware of the numeric coding for each group, will create the randomization sequence using an online random number generator (https://www.graphpad.com/quickcalcs/randomize1/, accessed on 15 December 2021) with a 1:1 allocation, using random block sizes of 12. Researchers 2, 3, and 4 are blind to the block size used in the randomization procedure.

A priori stratification was defined considering the three hospitals where data collection will take place, as well as two common comorbid conditions deemed as factors of poor prognostic outcomes in patients with DFUs, specifically chronic kidney disease (CKD) and peripheral arterial disease (PAD) [38,39], to ensure that distribution of patients between groups is balanced in terms of confounders. Thus, randomization is stratified according to (i) hospitals; (ii) CKD and its disease stages (without CKD/CKD stage 1 and 2/CKD stage 3 and 4); and (iii) PAD (without PAD/with PAD), in a total of 12 possible strata.

Participants’ blinding will be maintained throughout the conduct of the trial, whereas Researchers 1, 2, and 3 will be aware of the allocation since they are responsible and will conduct the TG1 and ACG sessions. Quantitative data analysts will be blinded to participant allocation. The randomization process will be conducted at the end of each week to reduce the time interval between the randomization and the beginning of interventions.

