## 3. Outcomes and Measures

### 3.1. Participant Timeline

Participants in the intervention and control groups will be assessed at the pre-intervention baseline (T0), at the end of the intervention/two months later at post-test (T1), and six months after T1 at the follow-up (T2). Data will be collected through face-to-face interviews conducted by health psychologists (Researchers 1, 2, and 3). Regarding the biochemical sample collection (biochemical parameter, inflammatory and angiogenic markers, miRNAs, and immune cells), a blood sample will be collected during the consultation at the T0, T1, and T2 assessment moments (Table 1).

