#### 4.1.2. Control Groups

Participants in the ACG will receive neutral guided imagery sessions, i.e., sessions focused on the patient’s daily life before the DFU. Neutral sessions are conducted by Researchers 1, 2, and 3 following a scripted protocol that includes four biweekly sessions of approximately 45 min, each one dedicated to a different topic (family, work, friends, and leisure). Initially, the participant will be asked to choose a specific event related to the topic of the session, positive or negative, without telling the researcher which event he/she thought about. Then, the participant will answer several questions regarding the episode to promote a more detailed reconstruction of the event, being instructed to only think about the answers and not to reply orally. When the whole episode is remembered, the participant will be asked to tell what he/she imagined/remembered regarding each of the questions. The goal of the placebo sessions is to control for the effect of the received attention, from psychologists and hypnotherapists, on patients in the treatment groups. It is possible that the privileged contact may positively influence the patient’s healing process. Therefore, the attention control condition will allow us to differentiate between the impact of interventions versus the attention given to the ACG.

Participants in the PCG will not receive any intervention besides the standard of care medical/nurse treatment. Both passive and active control patients will complete the same outcome questionnaires as the participants allocated to the interventions, at the same time intervals.

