### 4.2. Adherence to the Treatment Plan

Patients will be fully informed about the study goals, procedures, and potential benefits that may arise from the results of the DFU treatment. Assessment moments, intervention, and placebo sessions will be scheduled for diabetic foot appointment days so that patients will not have to go to the hospital on purpose to participate in the study. Before the appointment day, Researchers 1, 2, and 3 will call patients to remind them of their appointment with the research team for the purpose of the study. Participants will be asked to complete the last assessment (T2) even if they miss the mid-term assessment (T1).

To engage the health professional staff (e.g., physicians, nurses, podologists), meetings will be held with the physicians responsible for the multidisciplinary consultation of diabetic foot and head nurses (in the three hospitals involved in the study), in order to introduce the study and clarify any questions that may arise.

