## Figures and Tables

**Figure 1 ijerph-19-08556-f001:**
[figure not shown]
Study design and CONSORT flow chart.

**Table 1 ijerph-19-08556-t001:** Schedule of enrollment, interventions, and assessments of the PSY-DFU study, following the Standard Protocol Items Recommendations for Interventional Trials (SPIRIT) guidelines.

TIMEPOINTS	Enrollment	Allocation	Pos-Allocation			Follow-Up
		T0	T0	T1	2 Weeks after T1	T2
Eligibility	X					
Informed consent	X					
Allocation		X				
INTERVENTIONS			[figure not shown]			
PMR + GI (TG1)						
H + GI (TG2)						
Control groups			[figure not shown]			
Active (ACG)						
Passive (PCG)						
ASSESSMENTS						
Sociodemographic data			X			
Health literacy			X			
Clinical data (PEDIS)			X	X		X
DFU evolution/healing ^a^			X	X		X
Impact of DFU on QoL			X	X		X
Mental and physical QoL			X	X		X
Perceived stress			X	X		X
Psychological morbidity			X	X		X
DFU representations ^a^			X	X		X
Blood pressure ^b^			X	X		X
Heart rate ^b^			X	X		X
Biochemical parameter			X	X		X
Inflammatory markers			X	X		X
Angiogenic markers			X	X		X
miRNAs			X	X		X
Immune cells			X	X		X
Semi-structured interviews					X	

QoL—quality of life; PMR + GI—progressive muscular relaxation with guided imagery; H + GI—hypnosis with guided imagery; ACG—active control group; PCG—passive control group; PEDIS—Perfusion, Extent, Depth, Infection, and Sensation; DFU—diabetic foot ulcer. ^a^ In T1 and T2, when the DFU is healed, the DFU progression and DFU representations are not assessed. ^b^ Blood pressure and heart rate are assessed before and after each intervention (PMR + GI and H + GI) and placebo (ACG) session.

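### Participant blinding is claimed for the whole trial but cannot hold for the passive control group, and allocation-aware therapists collect the self-reported outcomes

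*Protocol article*

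**What the plan says.** Section 2.2 labels the study a "participant-blinded, sham-controlled, cluster randomized controlled trial (RCT"). Section 2.4 repeats that participants' "blinding will be maintained throughout the conduct of the trial, whereas Researchers 1, 2, and 3 will be aware of the allocation". The blinding claim carries no exception for any arm, and the reason given for the researchers' awareness is that they run the TG1 and ACG sessions. The quantitative analysts are to be blinded.

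Section 3.1 gives the same three people the assessments: "Data will be collected through face-to-face interviews conducted by health psychologists (Researchers 1, 2, and 3").

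On the passive arm, Section 4.1.2 states: "Participants in the PCG will not receive any intervention besides the standard of care medical/nurse treatment". On what patients are told, Section 4.2 states: "Patients will be fully informed about the study goals, procedures, and potential benefits".

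Sections 3.3.3 and 3.3.4 make the DFS-SF and SF-36 self-reported primary outcomes. PSS, HADS and IPQ-B are patient-answered secondary outcomes (Sections 3.4.1 to 3.4.3). Hypnosis is delivered by three hypnotherapists from outside the study (Section 4.1.1).

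**The concern.** Two separate things are at issue.

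The first is the blinding claim itself. A patient who knows that the study offers sessions, and is offered none, can tell which arm this is. For every comparison with the PCG, the trial lacks a property that it says it has.

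The second is who asks the questions. People who know the allocation, and who have treated some of the patients, collect answers on quality of life, stress and mood. Patients may answer more favourably to someone who has spent four sessions with them, and an interviewer who knows the arm may prompt differently. Blinding the analysts does not remove bias that is already in the answers.

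What is at stake is the reading of any QoL or distress difference. Against the PCG, it could reflect expectation and contact with the interviewer as well as an intervention effect. The relaxation-versus-hypnosis comparison, which Section 7 presents as the question the results will answer, also has a different interview setting in each arm.

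**Working it through.** The point rests on comparing sections; the plan gives no figure to reproduce.

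**Step 1: can participant blinding hold?** Sections 2.2 and 2.4 claim it for all participants. Section 4.1.2 gives the PCG no session of any kind, and Section 4.2 has patients informed of the procedures. The PCG is therefore open. TG1, TG2 and ACG each receive four sessions of about 45 minutes every two weeks (Sections 4.1.1 and 4.1.2), so blinding among these three is possible, depending on how the sessions are described to patients.

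**Step 2: who treats and who interviews?** Therapists are Researchers 1 to 3 for TG1 and ACG, external hypnotherapists for TG2, and nobody for the PCG. Interviewers are Researchers 1 to 3 for all arms. Section 4.1.1 has them run TG1 sessions in their respective hospitals, which suggests one per site. The interviewer may then often be the patient's own therapist, although Section 3.1 does not say who interviews whom.

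**Step 3: consequence for each contrast on self-reported outcomes.**

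| Contrast | Participant blinding possible? | Interviewer may be own therapist | Same in both arms? |
|---|---|---|---|
| TG1 vs ACG | Yes | Both arms | Yes |
| TG2 vs ACG | Yes | ACG only | No |
| TG1 vs TG2 | Yes | TG1 only | No |
| TG1 vs PCG | No | TG1 only | No |
| TG2 vs PCG | No | Neither arm | PCG has no therapist at all and knows it |
| ACG vs PCG | No | ACG only | No |

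**Step 4: size.** The document gives no basis for the size of a reporting shift. Only the sensitivity of a comparison to one can be shown, under assumed values. Take 42 patients per group (Section 5.1), no true effect, a two-sided 5% z-test and an assumed differential shift of b standard deviations. With δ = b / √(2/42) = b / 0.218, the rejection rate is 1 − Φ(1.96 − δ) + Φ(−1.96 − δ).

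| Assumed shift b (SD) | δ | False-positive rate |
|---|---|---|
| 0 | 0 | 5% |
| 0.1 | 0.46 | 7.4% |
| 0.2 | 0.92 | 15% |
| 0.3 | 1.37 | 28% |
| 0.4 | 1.83 | 45% |

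These rows illustrate the mechanism and do not estimate the bias in this trial.

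**The case against.** The best defence is that the design already contains the main safeguard. Section 4.1.2 says that the ACG exists to separate the intervention from the attention that comes with it. Because Researchers 1 to 3 deliver both TG1 and ACG, the interviewer effect is balanced in that comparison. This stands, and it is why the ACG contrasts should carry the conclusions. It does not rescue the PCG contrasts, and it covers TG2 only in part.

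Section 3.3.3 can also be read as having patients fill in the DFS-SF themselves, so self-completion may be partly in place. That is possible, but Section 3.1 describes data collection as interviews, and the two are not reconciled.

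Several stronger readings are tempting but not supported:

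- *That Section 7 contradicts the blinding claim.* It concedes incomplete blinding, but that fits Section 2.4, where the researchers know the allocation. The real conflict is between Sections 2.2 and 2.4 on one side and Section 4.1.2 on the other.
- *That baseline was taken after allocation, because Table 1 shows T0 under "Pos-Allocation".* T0 appears under the allocation column too, and the table layout as extracted is unreliable. HADS and PSS decide eligibility (Section 2.3), so they must precede randomization, and Section 3.1 calls T0 pre-intervention.
- *That patients in the session arms know which sessions are placebo.* Being informed of goals and procedures does not show this.
- *That the bias can be scaled against the planning difference of 1.93 with SD 6.* Section 5.1 does not name the outcome behind those figures, so they cannot be set against a shift in QoL or stress.
- *That wound scoring is affected.* RESVECH is completed by the physician or nurse (Section 3.3.1), and nothing says that they are told the arm. The interview route does not reach the blood markers either.

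**Conclusion.** The concern holds in two parts. The unqualified statement of participant blinding is wrong for the PCG. The collection of DFS-SF, SF-36, PSS, HADS and IPQ-B by allocation-aware staff leaves those outcomes open to a bias that differs by arm. Only TG1 versus ACG is balanced with respect to who treats and who interviews.

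The size cannot be computed from the document. The first part assumes that PCG patients infer their arm from being offered no session, which is an inference but hard to avoid without a sham. The second assumes that an interviewer's role can shift self-reported answers; how far depends on how much is self-completed in practice. The point should be put right but does not undermine the trial as a whole, since the wound score and blood markers lie outside it.

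**What to change.** - In Sections 2.2 and 2.4, limit the participant-blinding claim to TG1, TG2 and ACG, and state that the PCG is open.
- In Section 5.2, label PCG contrasts on self-reported outcomes as open-label. Base attention-controlled conclusions on those outcomes on TG1 versus ACG and TG2 versus ACG, noting for the latter that only ACG patients may be interviewed by their own therapist.
- In Section 3.1, have patients complete the T1 and T2 self-report forms themselves and seal them. Where help is needed, record that the form was completed with assistance.

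Using a researcher who did not treat the patient is a weaker remedy. With what looks like one researcher per hospital it could mean travel between sites, and under Section 2.4 the substitute would still know the allocation.

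The cost is wording and a change in form handling, with no new arm, patients or staff. Some items may be left blank, and patients with low literacy will still need a reader. Section 7 speaks of compliance problems already met, so recruitment may have begun. A change now would mix completion modes between earlier and later patients, so the date of change should be recorded.

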## 3. Outcomes and Measures

### 3.1. Participant Timeline

Participants in the intervention and control groups will be assessed at the pre-intervention baseline (T0), at the end of the intervention/two months later at post-test (T1), and six months after T1 at the follow-up (T2). Data will be collected through face-to-face interviews conducted by health psychologists (Researchers 1, 2, and 3). Regarding the biochemical sample collection (biochemical parameter, inflammatory and angiogenic markers, miRNAs, and immune cells), a blood sample will be collected during the consultation at the T0, T1, and T2 assessment moments (Table 1).

### 3.2. Characteristics of Patients

Sociodemographic and clinical characteristics of all participants will be assessed.

#### 3.2.1. Sociodemographic Characteristics

Sociodemographic data will be collected prior to intervention through the Sociodemographic Questionnaire, a questionnaire developed for the purposes of this study that includes variables such as gender, age, education, residence, marital and professional status, having (or not) an informal caregiver, socioeconomic level, smoking history, and alcohol intake, among others.

#### 3.2.2. Clinical Information

Clinical data will be collected through the Clinical Questionnaire, developed specifically for this study, to be completed by the patients’ physician or nurse in the three assessment moments. This questionnaire asks about the type and duration of diabetes, complications associated with diabetes, diabetic foot type, DFU location and duration, concomitant treatment, ulcer healing time, and new DFUs. The clinical questionnaire also includes the Perfusion, Extent, Depth, Infection, and Sensation (PEDIS) classification system, proposed by the International Working Group of the Diabetic Foot, thus gathering information regarding the five most important categories to evaluate the DFU stage and progression [40].

### 3.3. Measures of Primary Outcomes

Primary outcomes are DFU healing, physiological indicators of healing prognosis, DFU impact on QoL, and physical and mental QoL.

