#### 3.3.1. Degree of DFU Healing

Wound healing is defined as the complete epithelization of the wound and is assessed through the RESVECH 2.0-PT [41], a useful and validated tool to monitor the progression of chronic wounds of any etiology through six main parameters: wound area, depth and involved tissues, wound margins, type of tissue in the wound bed, levels of exudates, and presence of signs of infection/inflammations. This questionnaire will be filled out by the participant’s physician or nurse at the end of consultations to monitor DFU progression. Scores range from 0 to 35, where zero indicates complete healing and 35 corresponds to the worse possible wound.

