#### 3.3.2. Physiological Indicators of Healing Prognosis

Physiological indicators include a biochemical parameter (HbA1c), inflammatory (IL-6, TNF-α, lymphocyte populations) and angiogenic (VEGF) markers, miRNAs (miRNA-21, miRNA-155), and immune cells (lymphocytes T effective and naïve). The quantification of HbA1c in the plasma will be performed using the competitive inhibition enzyme immunoassay Cloud Clone Corp. The quantification of the plasma inflammatory cytokines levels (IL-6) and tumor necrosis factor (TNF-α) will be performed using a LEGENDplex™ Human Angiogenesis Panel 1 Mix and Match (9-plex). Blood lymphocyte populations will be assessed in the whole blood by flow cytometry and an automated hematological cell counter. Levels of VEGF will be assessed through the serum by ELISA from Cell Signaling Technology. miRNA-21 and miRNA-155 will be assessed through blood collected in a tube from Qiagen (PAXgene Blood RNA Tubes, Qiagen, Hombrechtikon, Switzerland), and subsequently, the RNA will be converted into cDNA by “miScript Reverse Transcription Kit” (Qiagen). Amplification of miR-21 will be done through the light Cycler system with SYBR Green PCR Kit. The control gene will be the RNU6B. Immune cells will be calculated through the ratio of lymphocyte effectors CD4/CD8 to lymphocyte naïve CD4/CD8 cells. Blood samples will be collected and processed in the clinical laboratory of two of the three hospitals where data collection will take place.

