#### 3.3.3. Impact of the DFU on QoL

The impact of the DFU on patients’ QoL will be assessed through the Diabetic Foot Ulcer Scale-Short Form (DFS-SF) [42], a self-report questionnaire to be fulfilled by participants to evaluate the effect of the DFU on patients’ general QoL.

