#### 3.3.4. Physical and Mental QoL

Patients’ physical and mental health-related QoL will be assessed through the Short-Form Health Survey (SF-36) [43], a self-report questionnaire administered to participants.

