### 5.2. Data Analysis

The baseline data of the treatments and control groups will be compared using the chi-squared test for binary variables and the independent sample t-test for continuous variables. To prevent overestimating the impact of both interventions, an intention-to-treat approach will be assumed to evaluate the impact on the primary and secondary outcomes. The comparison between the treatment groups versus control groups over time (differences between and within) will be performed through mixed general linear models of analysis of variance for repeated measures. Effect sizes (Cohen’s d coefficient) will also be provided between T0 and T1, T1 and T2, and T0 and T2 to determine if the intervention shows any treatment effect. A significance level of 0.05 will be set for a two-sided test, and the 95% confidence interval will be calculated. In addition, time to complete wound healing and time to favorable healing prognosis (based on the wound size) will be estimated using survival analysis, specifically, single variable and multivariable Cox proportional hazard ratio regression models and Kaplan–Meier plots. All previous analyses will include the DFU stage at the baseline as a control variable. Other confounding clinical factors associated with the outcome variables will also be considered in the statistical analysis.

The data will be analyzed using the Rstudio, R version 3.6.2 (R Core Team, Vienna, Austria) and the SPSS statistics, v. 24.0 (IBM Corp., Armonk, New York, NY, USA).

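### About 11 to 12 primary measures are unranked under a single 0.05 level, so the chance of at least one false-positive primary result is about 43–46% with one independent test each

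*Protocol article*

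**What the plan says.** Section 3.3 lists the primary outcomes as a group: "Primary outcomes are DFU healing, physiological indicators of healing prognosis, DFU impact on QoL, and physical and mental QoL". The subsections say what is measured:

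- **Section 3.3.1, healing:** the RESVECH 2.0-PT score. "Scores range from 0 to 35, where zero indicates complete healing and 35 corresponds to the worse possible wound".
- **Section 3.3.2, physiology:** "Physiological indicators include a biochemical parameter (HbA1c), inflammatory (IL-6, TNF-α, lymphocyte populations) and angiogenic (VEGF) markers, miRNAs (miRNA-21, miRNA-155), and immune cells", the last being a ratio of effector to naive lymphocytes.
- **Section 3.3.3, ulcer-specific quality of life:** the DFS-SF.
- **Section 3.3.4, generic quality of life:** the SF-36, physical and mental.

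The Abstract repeats the set without an order. On significance, section 5.2 says: "A significance level of 0.05 will be set for a two-sided test, and the 95% confidence interval will be calculated". It plans repeated-measures mixed models comparing treatment with control groups over time. It also plans Cohen's d for the three intervals between visits. Section 5.1 bases the sample size on one difference (1.93, SD 6) between treatment and passive control, at 5% significance.

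**The concern.** A primary outcome fixes in advance the result on which the trial will be judged. Here about a dozen measures hold that status equally, and each could be declared significant at 0.05. The 5% error rate then applies to each measure and not to the statement that an intervention improved a primary outcome. If neither intervention works, one cytokine, one microRNA or one quality-of-life score could still fall below 0.05 by chance and be reported as a positive primary finding. The sample size calculation is built around one comparison, so it gives no basis for reading the other measures as confirmatory.

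**Working it through.** **The plan's own figure.** Section 5.1 gives a difference of 1.93, SD 6, 80% power and 5% significance. The two-sided formula for comparing two means gives

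n = 2 × [6 × (1.960 + 0.842) / 1.93]² = 151.7, rounded up to 152,

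and 152 × 1.11 = 169. Both printed numbers reproduce. The calculation uses one comparison at an unadjusted 5%. (The formula's 152 is a number per arm, but the article uses it as the total. That is a separate problem, mentioned here only because it limits what the fix can achieve.)

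**Count of primary measures (sections 3.3.1 to 3.3.4).**

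| Domain | Measures | Number |
|---|---|---|
| Healing | RESVECH | 1 |
| Physiology | HbA1c, IL-6, TNF-α, lymphocyte populations, VEGF, miRNA-21, miRNA-155, effector/naive ratio | 8 |
| Ulcer-specific QoL | DFS-SF | 1 |
| Generic QoL | SF-36 physical, SF-36 mental | 2 |
| Total | | 12 |

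If the lymphocyte populations and the immune-cell ratio are one measure, the total is 11. If several lymphocyte populations or DFS-SF subscales are analysed separately, it is more than 12.

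**One test per measure, no true effect.** With k independent tests, the chance of at least one false positive is 1 − 0.95^k:

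- k = 11: 1 − 0.95^11 = 43.1%
- k = 12: 1 − 0.95^12 = 46.0%
- k = 4 (one test per domain): 1 − 0.95^4 = 18.5%

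The article gives no correlations between measures, so 0.3 and 0.6 are assumed as a range. For equally correlated normal test statistics the results are:

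| Correlation | 11 measures | 12 measures |
|---|---|---|
| 0 | 43% | 46% |
| 0.3 | 37% | 40% |
| 0.6 | 26% | 28% |

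**If arm comparisons are also tested separately.** The aims set two treatment groups against two control groups, giving 2 × 2 = 4 comparisons per measure. These share arms: with equal arms, two comparisons with one arm in common correlate at 0.5 in absolute value, and those with none in common are uncorrelated. They cannot be treated as 48 independent tests. Simulating four equal arms, 12 measures and one visit gives about 88%, 82% and 66% at correlations of 0, 0.3 and 0.6. This is a conditional figure, because section 5.2 does not say that the four comparisons are tested separately.

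**The case against.** There are five fair points on the other side.

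- **The analysis described is a model, not a list of tests.** Section 5.2 reads most naturally as one repeated-measures model per outcome. It attaches the visit intervals to Cohen's d and not to separate tests, although it says these serve to judge whether there is a treatment effect. A reader might infer 48 tests (12 measures by four comparisons), or 96 with two visits, and conclude that a false positive is more likely than not. The article does not set out that scheme. With one test per measure the risk stays below 50%. This objection stands, and the point rests on one test per measure.
- **A multiplicity procedure may sit in an analysis plan that is not shown.** This stands for the choice of method, and the absence of a method is not the finding. It does not reach the unranked primary set or the single 0.05 level, which the article itself fixes.
- **The count is uncertain.** It is, by one measure downwards, and that moves 46% to 43%. Subscales or separate cell populations would move it up.
- **The measures are correlated.** They probably are. Even at an assumed 0.6 the risk is about five times the nominal 5%.
- **The choice of contrast is not obvious.** Section 5.1 sizes the trial against the passive control, but section 4.1.2 explains that the active control is there to separate the intervention's effect from that of attention. Making the passive control the only primary comparator would give up that separation. This stands, and the fix leaves the choice to the sponsor.

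**Conclusion.** The concern holds in limited form. The article declares about 11 to 12 primary measures of equal standing and one two-sided 0.05 level. If neither intervention works, the chance of at least one significant primary measure is about 43–46% under independence, and about 40% and 27% at assumed correlations of 0.3 and 0.6. This rests on one test per measure and on equal correlation between measures. The 66–88% range applies only if the four treatment-against-control comparisons are each tested at one visit, which the aims imply but the analysis section does not state. The article therefore does not support saying that a false-positive primary result is more likely than not under the analysis as written. It does support saying that a significant result on some primary measure would be weak evidence that an intervention works.

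**What to change.** Amend sections 3.3 and 5.2, and update the registry entry, before unblinding:

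1. **Name one primary endpoint at one time point.** An example is the RESVECH total score at T1, after confirming that the 1.93 and 6 in section 5.1 refer to that score. State that a healed ulcer scores 0, because footnote a of Table 1 says progression is not assessed once the ulcer has healed.
2. **Rank the rest.** Make the DFS-SF and SF-36 key secondary outcomes in a fixed testing order. Make the biomarkers secondary outcomes, reported with confidence intervals and false-discovery control.
3. **Pre-specify the primary contrast or contrasts.** The sponsor should weigh the passive control, used for sizing, against the active control, which isolates attention. If more than one contrast is primary, apply Holm at an overall 0.05 across them.

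No extra patients, visits or data are needed, and every outcome is still reported. The cost is that a result confined to biomarkers or quality of life can no longer be claimed as primary, and Holm lowers the power of each contrast somewhat. The change does not cure the separate sample-size shortfall: 152 in total is 152 / 4 = 38 per arm, with about 29% power for a single pairwise contrast at 0.05 on the plan's own 1.93 and 6.
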